### Aim four: cost analysis

We will evaluate the effectiveness of SWPBIS with C + C as compared to SWPBIS with C in increasing procedural and process fidelity and in reducing ODRs and improving school climate, and children’s grades, diagnostic status, symptom severity and impairment; and the effectiveness of SWPBIS with C + C as compared to SWPBIS with C. An incremental cost-effectiveness ratio [116] will be constructed for each intervention (SWPBS with C + C for Tier 1, SWPBS with C for Tier 1, SWPBS with C + C for Tier 2, SWPBS with C for Tier 2). The denominator of the cost-effectiveness ratio is the difference between the effectiveness of the intervention and control groups (accounting for baseline levels) on designated measures of fidelity and student outcomes (*e.g.*, student grades). The numerator of the cost ratios is the difference in mean costs for intervention and control groups (accounting for baseline levels). All costs associated with the program will be set at $0 at baseline. Costs for interventions will include: initial development of the leadership team; initial training of the coaches (Tier 1) and clinical supervisors (Tier 2); initial training of the leadership team and school counselors; subsequent supervision of coaches and clinical supervisors; conducting groups with at risk children; and activities to maintain the SWPBIS program, including day-to-day implementation, ongoing training, data collection, and money for student incentives. Within each component, two main types of costs will be calculated: cost of physical materials used for training and interventions and costs associated with time spent by trainers and school personnel [117].

As an example, the cost-effectiveness ratio for fidelity will reveal how much it costs (or how much it saves) to increase fidelity among the study population by one point. Confidence intervals will be constructed to determine the probability that the difference between two ratios indicates significant differences in cost-effectiveness for the target population. The ratios can then be ordered from lowest to highest to show which intervention is the most cost-effective for increasing the SET score. Administrators then have the information they need to determine if gains in fidelity are sufficient to justify marginal costs. In a similar manner cost-effectiveness ratios can be constructed for other targeted outcomes (*e.g.*, measures of school climate, child symptomatology, impairment, coping skills, symptom severity, and functioning) for comparisons in which the results indicate significant improvement in the intervention group as compared to the control condition.

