### Study aims

The specific aims of the study are:

1. To determine whether program content and process fidelity for Tier 1 (for all students) and Tier 2 (for at risk and high risk students) differ between schools receiving a higher level of support (Consultation plus Coaching, C + C) and schools receiving a lower level of support (Consultation, C) for program implementers.

2. To determine whether school climate, office discipline referrals, and participants’ diagnostic status, symptom and impairment severity, coping skills, and academic productivity differ between schools receiving different levels of support (C or C + C).

3. To assess changes in mental health disparities brought about by Tier 1 (perception of school climate, student suspension rates) and Tier 2 (proportion of students with unmet need), respectively.

4. To determine the incremental cost-effectiveness of SWPBIS C versus SWPBIS C + C.

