## Methods/Design

Six K–8 schools in the School District of Philadelphia were randomly assigned to either Consultation or Consultation plus Coaching (See Figure 2). A stratified random assignment list of schools to condition was generated using a computerized random assignment program [77]. Schools were stratified to group one if their baseline School Climate (CREST) scores were below the median CREST scores or to group two if the CREST scores ≥ the median value. The units of analyses for Tier 1 are all of the students in those K-8 schools (650 per school), leadership team members (eight per school) and other school staff (30 per school). The units of analyses for Tier 2 are the children meeting criteria for inclusion in one of the GCBT groups (enroll a total of 367 students assuming a 17% dropout; approximately 51 eligible students per school), the school counselors (two per school) conducting the GCBT groups, and the groups themselves (14 per school; see Table 1).

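### Aim four plans a separate incremental ratio for C and for C + C against a control the trial does not have, ranks those ratios, and screens the other outcomes by significance

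*Protocol article*

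**What the plan says.** The Study aims section states the fourth aim as: "To determine the incremental cost-effectiveness of SWPBIS C versus SWPBIS C + C". Methods/Design gives the arms: "Six K–8 schools in the School District of Philadelphia were randomly assigned to either Consultation or Consultation plus Coaching". Table 1 has columns for these two support levels and their total only, and both arms receive SWPBIS.

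The section Aim four: cost analysis opens with the same contrast: "We will evaluate the effectiveness of SWPBIS with C + C as compared to SWPBIS with C in increasing procedural and process fidelity". It then changes frame:

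- **Ratios to be built.** "An incremental cost-effectiveness ratio [116] will be constructed for each intervention (SWPBS with C + C for Tier 1, SWPBS with C"; the list continues with C for Tier 1 and with both support levels for Tier 2, which makes four ratios.
- **Definition.** "The denominator of the cost-effectiveness ratio is the difference between the effectiveness of the intervention and control groups (accounting for baseline levels"). The numerator is the matching difference in mean costs. Programme costs are set to $0 at baseline.
- **Use.** Confidence intervals are planned for the difference between two ratios. Then: "The ratios can then be ordered from lowest to highest to show which intervention is the most cost-effective".
- **Other outcomes.** After fidelity, the worked example, ratios can be built for the remaining outcomes "for comparisons in which the results indicate significant improvement in the intervention group as compared to the control condition".

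The section does not say who the control group is.

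**The concern.** An incremental ratio needs a comparator. With two arms there is one increment per tier, C + C minus C. A separate incremental ratio for C has no randomised comparator, yet the ranking step needs a ratio for each support level. Whoever runs this analysis must decide what control means, and the choice changes what is estimated.

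The significance condition is a separate problem. The effect difference is the denominator of the ratio. Keeping only significant differences keeps the ones that chance has made large, so the extra cost per unit gained looks too low. It also gives no ratio to outcomes on which the two arms perform alike, and those are the outcomes for which the cost difference should decide.

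The article says the results should help districts and policymakers choose a level of support, so the stated rules matter beyond the trial.

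**Working it through.** Aim four gives no cost, effect or power figure, so there is nothing of the plan's own to reproduce. The check has three parts.

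**1. Possible meanings of control**

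| Reading | C + C ratio | C ratio | Consequence |
|---|---|---|---|
| Control = C | (cost C + C − cost C) / (effect C + C − effect C), valid | (cost C − cost C) / (effect C − effect C) = 0/0 | Two of the four ratios do not exist; one ratio per tier, nothing to rank within it |
| Control = own baseline at $0 | cost C + C / gain C + C | cost C / gain C | Both exist, but as uncontrolled before/after averages |
| Control = schools without SWPBIS | no data | no data | No such group |

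**2. What ranking the averages conveys (second reading)**

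Assumed figures, in arbitrary cost units: C costs 10 and gains 10 points, so its average is 10/10 = 1.0. C + C costs 18.

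| C + C gain | C + C average | Increment, C + C minus C |
|---|---|---|
| 15 | 18/15 = 1.20 | 8/5 = 1.6 per extra point |
| 12 | 18/12 = 1.50 | 8/2 = 4.0 per extra point |
| 10.5 | 18/10.5 = 1.71 | 8/0.5 = 16 per extra point |
| 9 | 18/9 = 2.0 | 8/(−1) = −8: C + C costs more and does less |

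C ranks first in all four rows, while the price of an extra point runs from 1.6 to 16 and then to dominance. The order does not carry the quantity that aim four asks for.

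The incremental ratio also needs its two parts reported with it. An extra cost of $10,000 with 2 points less effect gives 10,000/(−2) = −$5,000 per point; a saving of $10,000 with 2 points more effect gives −10,000/2 = −$5,000 per point. One negative value can mean dominated or dominant. The section foresees possible savings, so this can arise.

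**3. Size of the significance filter**

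Inputs from the article: 3 schools per arm, 51 Tier 2 students per school (153 per arm), and student-level chi-squared tests of improved or not improved between C and C + C (Data analytic plan).

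Assumptions: 42.5% improved under C; a true difference of 10 or 20 points; school-level ICC of 0.02 or 0.05 (the sample size section mentions a school share below 5%); beta-binomial schools; two-sided 0.05; a fixed cost difference. A simulated trial is kept if the difference is significant and favours C + C. With true difference d and estimate D, inflation is the mean of D/d and the relative cost per unit is the mean of d/D, both over the kept trials.

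| True difference | ICC | Kept | Mean D/d | Mean d/D | Cost per unit too low by |
|---|---|---|---|---|---|
| 10 points | 0.02 | 44% | 1.7 | 0.62 | 38% |
| 10 points | 0.05 | 46% | 1.9 | 0.57 | 43% |
| 20 points | 0.02 | 86% | 1.1 | 0.99 | 1% |
| 20 points | 0.05 | 80% | 1.2 | 0.94 | 6% |

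The bias is large when the true difference is modest and small when it is large.

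**The case against.** The strongest reply is that this is loose wording in a condensed article. The stated aim and the first sentence of the cost section both name C versus C + C, and numerator and denominator are defined as between-group differences adjusted for baseline. Read control as the lower-support arm, and the C + C ratio in each tier is correct. This largely stands: a reader might infer that the trial cannot give a valid C + C versus C answer, and the documents do not support that. The data allow it and the stated aim points to it. What remains is that the section also lists C ratios, compares ratios with each other and ranks them, and none of that works within a tier under this reading.

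Three other stronger readings also fail:

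- *The ranking could put the worse option first.* This is not shown. In the worked case where C + C is dominated, C ranks first, as it should. The two results that share −$5,000 are alternative outcomes of one contrast and would never be ranked against each other; they show only that a negative ratio is ambiguous.
- *Aim four would be left empty for most outcomes.* Fidelity is exempt from the condition, the sentence on other outcomes is permissive, and the simulation covers one binary child outcome. It says nothing about climate or discipline referrals.
- *Few results would reach significance with six schools.* A school-level t-test on 4 degrees of freedom would pass only 11–48% of trials in these scenarios, but the plan uses student-level chi-squared tests for these comparisons. Whether those suit clustered data is a separate question.

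The choice of method for joint uncertainty can fairly be left to a full analysis plan. The comparator, the ranking and the significance condition cannot, because the article fixes them.

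**Conclusion.** The point holds as a defect in the stated procedure. Two of the four planned ratios either do not exist or are uncontrolled before/after averages; ranking does not yield the incremental quantity aim four asks for; and the significance condition makes the retained ratios too favourable to C + C.

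For a binary Tier 2 outcome under the planned test, the distortion runs from about 1% (20 points, ICC 0.02) to about 43% (10 points, ICC 0.05). That range rests on the assumed improvement rate, differences, ICCs and fixed cost difference, since the article gives none of them for this comparison. The comparator and ranking problems follow from the text alone. Because the right contrast is already stated elsewhere in the article and is estimable from the planned data, this should be corrected but does not undermine the trial.

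**What to change.** In Aim four: cost analysis:

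1. Name C as the comparator and delete the references to a control group or condition.
2. Replace the four ratios with one comparison per tier, C + C minus C. For every designated outcome, report the incremental cost and the incremental effect, whatever the significance of the effect.
3. Give their joint uncertainty in a way that respects the school clusters, and show both components so that a negative ratio can be interpreted.
4. Delete the ordering of ratios and the condition that improvement be significant.

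This is a change of wording and analysis only. The costs and outcomes by arm are already to be collected, so no new data are needed.

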### Examination of focus group results

As indicated, focus groups will be conducted with LTs to identify their perceptions of SWPBIS implementation in their schools. Sessions will be transcribed and analyzed qualitatively, based on grounded theory. Two RAs will read the transcripts independently and record all major themes on index cards. The RAs will present the data to the research team. The research team will then try to resolve any discrepancies between the RAs’ findings. Next, the RAs will examine the transcripts once again and identify the frequency of comments pertaining to each theme. The frequencies for RA one and RA two will be compared to check for inter-rater agreement. Standard frequency tables will be used to compare the relative frequency of endorsements for each theme. The agreement between the two RAs will also be checked by calculating the Kappa co-efficient.

### Sample size justification and statistical power

Sample size estimation was based on addressing the primary outcome, the participants’ diagnostic status (aim two). The statistical analysis will be McNemar tests for two correlated proportions (pre/post) between two groups. With a sample size of 300 students, the statistical test achieves 92% power to detect an odds ratio of three using a two-sided McNemar test with a significance level (α ) of 0.01. The odds ratio is equivalent to a difference between two paired proportions of 0.25, which occurs, for example, when the proportion among students diagnosed with a Positive anxiety/externalizing disorder at pre and improved to Intermediate at post (cell 1,2 in the 2X2 McNemar table) is 0.425 and the proportion among students diagnosed without Positive anxiety/externalizing disorder who became either Intermediate or Positive at post (cell 2,1 in the 2X2 McNemar table) is 0.175. Therefore, the proportion of discordant pairs is 0.60. We adjusted α level to 0.01 to account for the multiple 2X2 McNemar testing. We need to recruit six schools, grades four to eight,to be able to enroll 300 evaluable students who meet inclusion criteria. We assumed that the observed changes in students’ diagnostic status within schools are independent based on an evaluation of the FRIENDS program, in which ‘schools’ level accounted for less than 5% of the total variance across dependent measures.

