Changes from pre- to post- implementation in diagnostic status, symptom severity and impairment level, coping skills and academic productivity during Implementation across all schools, regardless of level of support, will be analyzed using McNemar tests. For each of the listed primary outcomes, a series of 2X2 tables will be constructed to test changes from pre- to post- in the pertinent categories using McNemar tests. Alpha level will be adjusted to 0.025 based on Bonferroni criteria for multiple comparisons. We will also use McNemar tests to test the hypothesis that the pre- to post- level of improvement in diagnostic status, symptom severity, impairment level, coping, and academic productivity obtained during Implementation will be maintained during Sustainability among schools receiving C + C.

We would like to determine whether pre- to post- improvement in diagnostic status, symptom severity, impairment level, and academic productivity differ by support condition during the implementation phase. In addressing this research question, and for the sake of simplifying the statistical analysis, each student will be categorized as either improved or not improved based on change from pre- to post-. A category one will be assigned if a student’s diagnostic status, for example, changes either from positive to intermediate, intermediate to negative, or positive to negative. Otherwise a score of zero will be assigned. Similar coding will be used for symptom severity, coping, impairment level, and academic productivity. We will use chi-squared tests to compare the proportion of (yes/no) for each of the primary outcomes between C and C + C type of supports. To examine changes in the rate of ODRs between baseline and follow up during each school year, the number of students with at least one ODR will be defined at baseline and at the follow up and a 95% confidence interval for such changes will be constructed for each of the five years.

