### Challenges and limitations

Implementing SWPBIS with mental health supports in under-resourced urban schools presents a number of challenges. In our pilot study where we developed and piloted the interventions, we faced repeated leadership changes at the district level, staff turnover at the school level, and limited parent participation [74]. However, we also found strong and consistent support among second-level administrators (*e.g.*, regional superintendents) at the District level and committed leadership teams that were able to recruit new members who functioned effectively. With the lessons learned from our pilot study, we are able to more effectively support the schools in successfully implementing SWPBIS while receiving either level of support. We have redoubled our efforts at helping schools to increase parental collaboration and support, which lead to more parent participation. We have also designed the implementation strategy to fully utilize existing policy and infrastructure (*e.g.*, implementation of District-wide practices to promote students’ success; utilizing school counselors and school facilities for Tier 2 interventions) to limit strain on resources so that the proposed program will be sustainable.

A limitation is that we are conducting the study in six schools within a single school district (though it is one of the largest and most diverse school districts in the country), which limits generalizability to schools in different parts of the country. Including a relatively small number of schools limits our ability to examine the clustering effect of school classes and schools. In this study, the unit of randomization is the school but the unit of analysis (aim two) is the student. A cluster randomized approach would have been an appropriate design if a much larger number of schools were included in the study. However, it is anticipated that the degree of similarity in treatment response among students within a class will be poorly correlated, and therefore the intraclass correlation coefficient within clusters will be small and its effect on the overall variance between schools would be minimal. However, an appropriate cluster analyses will be conducted using nested analysis. The NESTED Procedure of SAS [115] is an example of such analysis. We expect that our findings will inform implementation research in schools and procedures to be incorporated into larger-scale trials in urban schools in the future.

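### The 92% power tied to aim two is for a pre/post McNemar test, not the randomised C v C + C comparison; it assumes no clustering within schools and does not follow from its own inputs

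*Protocol article*

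**What the plan says.** In the protocol article, Sample size justification and statistical power states: "Sample size estimation was based on addressing the primary outcome, the participants’ diagnostic status (aim two"). Study aims defines aim two as whether diagnostic status and the other listed outcomes "differ between schools receiving different levels of support (C or C + C").

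The power section then says: "The statistical analysis will be McNemar tests for two correlated proportions (pre/post) between two groups". It opens the calculation "With a sample size of 300 students" and reports 92% power for an odds ratio of three at two-sided alpha 0.01, with discordant cells 0.425 and 0.175.

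The Data analytic plan keeps two analyses apart. Change from pre to post across all schools, "regardless of level of support, will be analyzed using McNemar tests", has its alpha set at 0.025. For the level of support: "We will use chi-squared tests to compare the proportion of (yes/no) for each of the primary outcomes between C and C + C". No power or between-arm difference is given for that second test.

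On clustering, the power section assumes that children's changes within schools are independent, because in an evaluation of FRIENDS the school "level accounted for less than 5% of the total variance across dependent measures". Challenges and limitations acknowledges that schools are randomised and students analysed, and expects the within-cluster correlation to be small, so that "its effect on the overall variance between schools would be minimal".

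**The concern.** The only power figure is attached to the aim that contains the randomised contrast, but it describes a different quantity. Power to detect that children improve over time, pooled over both arms, says nothing about whether they improve more under one level of support. The power section's wording merges the two questions.

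The independence assumption does not follow from its evidence. A school share of variance somewhere below 5% is small for one child, but its effect on the variance of a school mean grows with the number of children in the school.

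The trial is meant to tell districts whether the costlier support is worth buying. A null C v C + C result, read beside 92% power for aim two, could be taken as evidence that the cheaper support is as good. Three schools per arm do not support that reading.

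**Working it through.** **1. The stated 92%.** Inputs from the power section: cells 0.425 and 0.175, so difference d = 0.25 and discordant proportion pd = 0.60; two-sided alpha 0.01 (z = 2.576).

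Power = Φ[(d√n − z√pd) / √(pd − d²)], with z√pd = 1.995 and √(pd − d²) = √0.5375 = 0.733.

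- n = 300: (4.330 − 1.995)/0.733 = 3.19, power 99.9%. Continuity-corrected and exact versions agree.
- n = 150 (one arm's share): (3.062 − 1.995)/0.733 = 1.46, power 92.7%.

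So the stated value is close to what a single arm's children would give, which is still a within-arm pre/post figure. The cells give an odds ratio of 0.425/0.175 = 2.43. An odds ratio of 3 needs 0.45/0.15 (at 0.60 discordant) or 0.375/0.125 (at d = 0.25); both exceed 99.9% at n = 300.

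**2. Design effect.** About 51 children per school (Methods/Design). DE = 1 + (51 − 1) × ICC. The ICC values are assumptions spanning what the article allows; 0.05 is the upper bound, not an estimate.

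| ICC | DE | Effective n from 300 | Pre/post McNemar power, alpha 0.01 |
|---|---|---|---|
| 0 | 1.0 | 300 | 99.9% |
| 0.01 | 1.5 | 200 | 98% |
| 0.02 | 2.0 | 150 | 93% |
| 0.05 | 3.5 | 86 | 67% |

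These use the normal formula with n replaced by n/DE, with no further allowance for having only six schools.

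**3. The randomised comparison.** The article gives no between-arm effect, so these are assumptions: three schools per arm, 51 children each (153 per arm, Table 1), 42.5% improved in one arm, and a school-level test with 6 − 2 = 4 df.

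SE = √[(p₁q₁ + p₂q₂) × DE / 153]; power from the noncentral t with noncentrality (p₂ − p₁)/SE.

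Example, 42.5% v 62.5% at ICC 0.05: SE = √[(0.2444 + 0.2344) × 3.5/153] = 0.1047; noncentrality 0.20/0.1047 = 1.91; critical t = 2.776; power 31%.

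| ICC | Power, 20 points, alpha 0.05 | Power, 25 points, alpha 0.05 | Difference for 80% power, alpha 0.05 | Same, alpha 0.01 |
|---|---|---|---|---|
| 0.01 | 60% | 79% | 25 points | 37 points |
| 0.02 | 49% | 68% | 29 points | 41 points |
| 0.05 | 31% | 46% | 36 points | about 50 points |

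A student-level test that ignores clustering would show about 94% for the 20-point difference at alpha 0.05. From an assumed 60% base, the 80%-power differences at alpha 0.05 are about 23, 26 and 32 points.

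**4. Unadjusted chi-squared.** Its type I error at nominal 0.05 is about 2[1 − Φ(1.96/√DE)]: 11% at DE 1.5 and 29% at DE 3.5.

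**The case against.** The article is partly open about this. The Data analytic plan separates the pooled McNemar analysis from the C v C + C test. Challenges and limitations states the mismatch between units of randomisation and analysis, says that few schools limit the study of clustering, and promises a nested analysis. A careful reader need not take 92% as the power of the randomised contrast, and it would be wrong to say that clustering is ignored. But that section gives no power for the nested analysis, calls the clustering effect minimal, and leaves the 92% attached to aim two.

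The between-arm figures are conditional. The 42.5% base is borrowed from a McNemar cell and is not the improvement rate that the analysis plan defines. No alpha is stated for the chi-squared test; 0.025 and 0.01 both belong to McNemar. This stands, and is why ranges are shown.

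Three stronger readings are tempting and not supported:

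- That the pre/post analysis is underpowered. The 67% arises only at the ICC bound; at 0.01 and 0.02, power is at or above the stated 92%.
- That the design falls short of 92% for any between-arm effect. That depends on an effect the article never states: a student-level test at ICC 0 and alpha 0.01 has 97% for 25 points. With 4 df, a 25-point difference gives just under 92% at alpha 0.05 even at ICC 0.
- That schools are wrongly treated as independent of each other. Independence between schools is standard; the assumption at fault is independence of children within a school.

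**Conclusion.** The point holds. The 92% is tied to aim two but belongs to a paired pre/post test, and no power is stated for the randomised C v C + C comparison. This is a misattributed figure in the text, not a detail left to another document.

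Two faults lie inside the same calculation. Independence within schools is inferred from a bound that permits a design effect of up to about 3.5, so a minimal effect of clustering is not supported. And n, odds ratio, cells and stated power do not agree with one another, while alpha differs between the power section and the analysis plan.

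Under the assumptions in the working, the trial has 80% power at alpha 0.05 only for between-arm differences of roughly 25 to 36 percentage points from a 42.5% base, or 23 to 32 from a 60% base, and for larger ones at alpha 0.01.

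**What to change.** 1. Say that the McNemar figure covers pre/post change only. Restate it so that n, odds ratio, cells and alpha agree, settle 0.01 or 0.025, and allow for clustering: with the present cells, n = 300 and alpha 0.01, about 98%, 93% and 67% at ICC 0.01, 0.02 and 0.05.
2. Delete the independence assumption and state the design effect (1.5 to 3.5 over that ICC range). Amend the matching sentence in Challenges and limitations.
3. State the between-arm figure with its assumptions: three schools per arm, about 51 children each, a 4-df school-level test, and the chosen base rate and alpha. Over ICC 0.01 to 0.05 at alpha 0.05 this is about 25 to 36 points from a 42.5% base (23 to 32 from 60%); at alpha 0.01 it is about 37 and 41 points at ICC 0.01 and 0.02.
4. State that a null C v C + C result is not evidence that the two levels of support are equivalent, and report that comparison with cluster-adjusted confidence intervals.

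The cost is a rewritten power paragraph, matching edits to the limitations and the C v C + C analysis text, and a less favourable stated power. No schools or children are added.

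### The stated 92% power does not follow from its inputs: 300 children with discordant cells 0.425 and 0.175 give 99.9%, 92% needs about 150 children, and the cells imply an odds ratio of 2.43, not 3

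*Protocol article*

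**What the plan says.** All the inputs stand in one paragraph of the protocol article, under Sample size justification and statistical power. Diagnostic status is named there as the outcome that sizes the trial.

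- Sample, power and effect: "With a sample size of 300 students, the statistical test achieves 92% power to detect an odds ratio of three".
- Test and alpha: "using a two-sided McNemar test with a significance level (α ) of 0.01".
- Effect restated as a difference: "The odds ratio is equivalent to a difference between two paired proportions of 0.25".
- First discordant cell: "improved to Intermediate at post (cell 1,2 in the 2X2 McNemar table) is 0.425".
- Second discordant cell: "became either Intermediate or Positive at post (cell 2,1 in the 2X2 McNemar table) is 0.175".
- Discordant total: "Therefore, the proportion of discordant pairs is 0.60".

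The paragraph describes the McNemar tests as pre-post tests between two groups, and it assumes that changes within schools are independent. The Data analytic plan applies the Implementation-phase pre-post McNemar tests to all schools pooled, whatever the support level. It compares the two support conditions separately, with chi-squared tests on improved/not improved. Table 1 gives 153 Tier 2 students per arm and 306 in total.

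**The concern.** McNemar power is fixed by four things: the number of pairs, the two discordant cells, alpha and sidedness. The article prints all of them, so its power figure can be checked without assumptions. Two things look wrong. First, 300 pairs with a difference as large as 0.25 should give power far above 92%. Second, the odds ratio of three is called equivalent to cells whose ratio is not three.

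This paragraph is the only quantitative support for six schools and 300 evaluable children. If the sizing is for the pooled pre-post test, the 92% is wrong. If it is for one arm, the 300 is wrong. A reader who sees 92% beside the mention of two groups may also take it as power for Consultation versus Consultation plus Coaching. It is not: it describes change over time.

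**Working it through.** **Inputs**, all from the sample size section: p12 = 0.425, p21 = 0.175, two-sided alpha 0.01 (z = 2.576), n = 300, no design effect because independence is assumed.

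**Step 1: the cells.**
- Difference d = 0.425 − 0.175 = 0.25. Agrees with the article.
- Discordant total s = 0.425 + 0.175 = 0.60. Agrees.
- McNemar odds ratio = 0.425/0.175 = 2.43. The article says 3.

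An odds ratio of 3 requires p12 = 0.75s and p21 = 0.25s, hence d = s/2:
- keeping s = 0.60 gives cells 0.45/0.15 and d = 0.30;
- keeping d = 0.25 gives cells 0.375/0.125 and s = 0.50.

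Neither pair matches the printed cells.

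**Step 2: power at n = 300.** The normal approximation is

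power = Φ[(d√n − z√s) / √(s − d²)]

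with z√s = 2.576 × 0.7746 = 1.995 and √(s − d²) = √0.5375 = 0.7331.

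n = 300: (0.25 × 17.321 − 1.995)/0.7331 = 3.18, so power = 99.9%.

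The stated 92% is not reproduced.

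**Step 3: where 92% does appear.**

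n = 150: (0.25 × 12.247 − 1.995)/0.7331 = 1.45, so power = 92.7%.

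The exact column below is the binomial McNemar test averaged over the number of discordant pairs.

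| n | Normal | Continuity-corrected | Exact |
|---|---|---|---|
| 150 | 92.7% | 91.0% | 91.7% |
| 153 (one arm, Table 1) | 93.3% | 91.7% | 92.3% |
| 300 | 99.93% | 99.91% | 99.91% |

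The smallest n that reaches 92% is 147 (normal), 155 (continuity-corrected) or 152 (exact).

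**Step 4: can another reading recover 92% at n = 300?**
- *Alpha.* At n = 300, alpha 0.05 and 0.025 both give more than 99.9%, alpha 0.002 gives at least 99.5%, and alpha 0.001 gives 99.2%. No plausible alpha explains the gap.
- *Odds ratio of exactly 3.* Cells 0.375/0.125 or 0.45/0.15 give 99.99% or more at n = 300. At n = 150 they give about 96–98% and 99% respectively, so neither sample size yields 92%.
- *Odds ratio 3, n = 300, discordance left free.* Power of about 92% needs s ≈ 0.21 and d ≈ 0.105: (0.105 × 17.321 − 2.576 × √0.21)/√(0.21 − 0.105²) = 1.43, or 92.4%. This contradicts the printed 0.60 and 0.25.

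**The case against.** Five points can be made for the plan.

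1. *The error is in the safe direction.* This stands. On the article's inputs the pooled test has more power than claimed, and at 153 children per arm the exact power is 92.3%. On either reading, the planned sample delivers the stated power for the stated cells. That limits the practical consequence, but it does not make the paragraph correct.

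2. *The per-arm origin is inferred.* This also stands. The article never mentions 150. The printed cells reproduce 92% near 150, which makes that the likeliest explanation, but only the sponsor can confirm it. An alternative is that the headline sentence (300, odds ratio 3, alpha 0.01) is right and the cells, which are introduced as an example, are wrong. In that case both the stated difference and the stated discordance would have to be withdrawn.

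3. *The odds ratio of three might be marginal.* With the concordant cells unstated but summing to 0.40, the unpaired pre-post odds ratio for these cells lies between 2.78 and 3.48. It equals 3 when one concordant cell is 0.075: (0.50/0.50)/(0.25/0.75) = 3. So three could be a mislabelled marginal value. But the article attaches it to the McNemar test, where the odds ratio is the discordant ratio, and a marginal reading leaves the power error untouched.

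4. *A clustering allowance might be hidden in the 300.* With an assumed intraclass correlation of 0.02 and 50 children per school, the design effect is 1 + 49 × 0.02 = 1.98. The effective n is then 151.5 and power is 93.0%. The section rules this out by assuming independence.

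5. *The target is not wholly ambiguous.* The Data analytic plan does say that the Implementation pre-post tests are pooled. This stands in part: it makes 300 the natural n for that test, and the power for that n is 99.9%. The reference to two groups in the sample size section is what clouds it.

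**Conclusion.** The concern holds. The printed power, sample size, odds ratio and cells are mutually inconsistent. With the printed cells, two-sided alpha 0.01 and independence, power at 300 is 99.9%, about 8 percentage points above the stated 92%. The stated figure fits about 150 children (91.0–92.7% in the variants tabulated). The discordant-cell odds ratio is 2.43, not 3.

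The result rests only on figures in the article and the standard McNemar formulae, and the exact and approximate calculations agree. The per-arm origin is likely but not established. The finding does not show that the trial is underpowered for the pooled pre-post change. It also says nothing either way about power for the comparison of support conditions, which this calculation does not address.

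**What to change.** Rewrite the one paragraph after checking the original calculation.

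- State whether the calculation is for one arm or for all children pooled, and remove or explain the reference to two groups.
- If it is within one arm: give n as about 150 and keep power at about 92%.
- If it is pooled, as in the Data analytic plan: keep n = 300 and state power above 99% under independence.
- In both cases replace the odds ratio of three with 2.43, which agrees with the difference of 0.25 and the discordance of 0.60. If an odds ratio of 3 was really intended, change the cells, the difference and the power together.
- Say that the figure concerns pre-post change and is not power for Consultation versus Consultation plus Coaching.
- Report the power with an allowance for schools beside it. As an illustration for n = 300 with the printed cells and 50 children per school, assumed intraclass correlations of 0.01, 0.02 and 0.05 give 98.3%, 93.0% and 67.7%. The values are assumptions; the article says only that the school level explained under 5% of variance in an earlier evaluation.

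The cost is one reworded paragraph. Recruitment, alpha and the planned analyses need not change.
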